### Family setting

#### Newsletters

Nine newsletters per year (18 in total) will be sent home to parents providing project updates and tips on reducing their child's sedentary behaviors. The newsletters will support the key learning messages delivered to the children in the classroom and will help parents reinforce maintaining children's screen-time to a minimum. They will be translated into the most common languages spoken among the families with non-English speaking backgrounds. Newsletters will incorporate family based activities for parents to complete with their child and contain information about ways to reduce their child's screen time, including the effective use of rules (i.e., no television viewing during mealtimes, restrictions on small screen use, etc.).

#### Homework assignments

Homework tasks will be modified to reduce sitting time while completing them at home (e.g., complete worksheets while standing at the kitchen bench). Children will also be given homework tasks to complete with their parents; for example, to switch off the television for a whole weekend day and do something with their parents (a menu of alternative light-intensity activities will be provided).

### Physical activity intervention arm (PA-I)

Increasing or maintaining moderate- to vigorous-intensity physical activity (e.g., active play, organized and non-organized games) during recess and lunch breaks will be targeted in the school setting and time spent outdoors will be targeted in the family setting. The key mediators of change in physical activity will also be targeted (shown in Table 1).

### School setting

#### Curriculum-based program

As for SB-I, 18 key learning messages (9 lessons per year) modified from Switch-Play [44] but focusing on increasing physical activity will be delivered by teachers. Children will be encouraged to meet the national physical activity recommendations for young people of 60-minutes of moderate- to vigorous-intensity physical activity every day. All lessons will be developed in line with the Victorian Essential Learning Standards for year levels 3 and 4.

#### Physical activity during recess and lunch breaks

Physical activity will be promoted and encouraged during recess and lunch breaks. Based on previously efficacious intervention strategies promoting physical activity during recess and lunch breaks [60], schools will be provided with sports equipment to make available for children to use in recess and lunch breaks, and teachers and peers will provide encouragement and support for active games.

#### Environmental cues and prompts

Signage will be used to promote physical activity in schools and will be regularly updated. Consistent with previously successful interventions [61], schools will select and receive novel line markings promoting active play in asphalt areas in the school playground. Each class will be provided with a set of pedometers for use during the key learning messages based on physical activity capability. Furthermore, the pedometers can be rotated throughout the class for children to gain awareness of their steps in different environments (e.g. weekday, weekend, school camp).

### Family setting

#### Newsletters

Eighteen newsletters (nine per year) will be sent home to parents providing project updates and tips on promoting their child's physical activity. The newsletters will support the key learning messages delivered to the children in the classroom and will help parents reinforce physical activity promotion at home. They will be translated into the most common languages spoken among the families with non-English speaking backgrounds. Newsletters will incorporate family-based activities for parents to complete with their child. For example, newsletters will contain information about activities to do at home and in their neighborhood (suitable for boys and girls). Parents will also be directed to the Kinect Australia website http://www.kinectaustralia.org.au/content/Public/Homepage.aspx and free Infoline, both of which contain information for parents on ways to engage their child in physical activity at home, ways to be active with their child, as well as identifying specific places in their own neighborhood where they can take their child to play (e.g., playgrounds, walking trails, local sports clubs).

#### Homework assignments

Homework tasks will be modified to incorporate physical activity and children will be encouraged to complete these tasks with their parents (e.g., go for a walk with their parents and write about where they went and what they saw; mathematics homework using their stride as the unit of measurement).

### Combined sedentary behavior and physical activity intervention arm (SB+PA-I)

Schools randomized to the combined SB+PA-I intervention arm will receive a blended version of the two interventions, but with the same intervention 'dose'. For example, when children in this arm complete a behavioral contract to switch off the television, they will be encouraged to participate in physical activity (SB-I children will not be directly encouraged to participate in activity when they switch off their television). The combined intervention arm will include 18 class lessons (9 per year), standing lessons and interruptions to children's classroom sitting time (short breaks), the promotion of physical activity during recess and lunch breaks, and 18 newsletters to parents.

### Control - usual practice

Schools assigned to the usual practice control group will be asked to continue their usual lesson delivery and will receive all intervention materials (apart from line markings) at the completion of the 12-month follow-up period

### Teacher training

In the first year of the intervention (2010), all participating year 3 teachers at intervention schools will be required to attend a professional development (PD) session. In the second year of the intervention (2011), all year 4 teachers will undergo the same training. There may be some teachers who teach both years of the intervention, or the second year may contain new teachers who have not been previously involved in the delivery of the intervention. The PD session will run for approximately two hours and will inform and/or refresh the teachers about the intervention including the aims, procedures of the study and strategies to be used. A mid-year morning tea meeting will be held with teachers to ensure that they are delivering the intervention as intended and to answer any questions or solve any difficulties they may be experiencing in intervention delivery. At the beginning of the third year (2012), all year 5 teachers at the intervention schools will be trained in their specific intervention components but will have no further contact or support from the study team throughout the year. This tapered approach will enable the maintenance of the strategies to be examined.

### Measurement protocol

Assessments will be conducted at baseline (Feb-May 2010), mid-intervention (Nov-Dec 2010), post-intervention (Nov-Dec 2011), and 12-months follow-up (Nov-Dec 2012). To minimize participant burden, blood pressure assessments will be taken at baseline, post-intervention and 12-months follow-up only, and blood samples will be taken at baseline and post-intervention only. All of the children's measurements (except the blood samples) will be conducted at school by trained research staff using regularly calibrated equipment. Children will complete the survey in small groups with trained research staff. The blood sample will be undertaken at a commercial pathology laboratory by a trained phlebotomist and the parent survey will be sent home to parents to complete.

### Primary outcomes

#### Sedentary time and physical activity

##### ActiGraph accelerometer

Sedentary time and physical activity will be objectively-assessed using the uniaxial function in the ActiGraph Model GT3X accelerometers http://www.theactigraph.com/. Children will wear the ActiGraph on a belt positioned over the right hip during waking hours (apart from during water-based activities) for eight days at each of the measurement points. Data will be collected in 15-second epochs. The movement count threshold for sedentary time will be set at 25 counts per 15-second epoch [62], and the number of breaks or interruptions to time spent sedentary will be defined as the frequency of occasions data exceeded 100 counts.min-1. The Freedson age-adjusted equation [63], will be applied to calculate the time spent in light (1.7-3.9 METS), moderate- (4.0-5.9 METs) and vigorous-intensity (≥6.0 METs) physical activity. We will also extract accelerometry data from specific times of the day (e.g., after-school hours, during class time) to identify when changes in sedentary time or physical activity may have occurred.

##### *activ*PAL™ inclinometer

A sub-sample of randomly selected children will concurrently wear a PAL Technologies Ltd, Glasgow, Scotland http://www.paltech.plus.com/products.htm inclinometer *activ*PAL™. The *activ*PAL™ is a small device (5 × 3.5 × 0.7 cm) weighing 20 g and is worn on a garter belt positioned at the mid-anterior aspect of the right thigh during waking hours (apart from water-based activities) for eight days at each of the measurement points. The following parameters will be calculated from this device: sedentary time (sitting/lying time); stand time (not walking); walk time; and sit-to-stand events. The device has been found to have acceptable validity in assessing these parameters in adults [64,65].

ActiGraph and *activ*PAL™ data validity criteria will be assessed prior to inclusion in analysis. A minimum of four valid days, including one weekend day will be required. To be included in analyses, a day will be considered valid if the child has at least eight hours of wear time per day or at least 50% wear time within periods of the day (e.g., classtime). Further, 20 minutes of consecutive zeros will be considered non-wear time. Recordings of over 16000 counts per minute (cpm) will be excluded as it indicates unit malfunction.

##### Survey measures

Behavioral information on the types of physical activities and sedentary behaviors in which children participate (not detectable by accelerometry or inclinometers) will be collected by a parental proxy-report version of the validated CLASS questionnaire [66]. Time spent outdoors will be assessed using a previously validated proxy-report measure [67].

### Secondary outcomes

#### Anthropometry: height, weight and waist circumference

Height will be measured to the nearest 0.1 cm using SECA portable stadiometers (mod 220). Weight will be measured to the nearest 0.1 kg using portable electronic Wedderburn Tanita scales. Two height and weight measurements will be taken and the average calculated. Where a discrepancy of over 1 cm or 1 kg is noted, a third measurement will be taken.

BMI (kg/m2) will be calculated and converted as recommended for analysis of longitudinal adiposity data [68]. This involves subtracting the sex-age population median (based on US data)[69] from the child's raw BMI score. Children will also be categorized as healthy weight or overweight/obese based on International Obesity Task Force definitions [70].

Waist circumference will be measured using a flexible steel tape at the narrowest point between the bottom rib and the iliac crest, in the midaxillary plane. If there is no obvious narrowing the mid-point between these two landmarks will be used [71]. Two waist circumference measurements will be taken and the average calculated. Where a discrepancy of over 1 cm is noted, a third measurement will be taken. Continuous data will be compared to UK charts [72]. Sex and age-specific waist circumference thresholds for children that correspond to clustering of cardiovascular disease risk factors will also be applied [71].

#### Blood pressure

After a quiet two-minute seated rest, children will have their blood pressure measured on their right arm using the OMRON HEM-907 automatic digital blood pressure machine. Three measurements will be taken one-minute apart on two occasions (one week apart). The first measurement on each occasion will be discarded. The remaining four measurements will be averaged to obtain systolic and diastolic blood pressure measurements.

#### Serum Biomarkers

A fasted, morning blood sample (16.5 ml) will be taken by a phlebotomist at a commercial pathology laboratory to assess children's cholesterol, high density lipoprotein (HDL) cholesterol, low density lipoprotein (LDL) cholesterol, triglycerides, glucose, insulin, C-reactive protein and 25-Hydroxy Vitamin D levels. Biomarkers will be taken at baseline and post-intervention data collection points only.

#### Survey measures

##### Mediators

Intrapersonal, interpersonal and environmental mediators of children's sedentary behaviors and physical activity will be assessed by parental proxy-report and child self-report survey (Table 1). Intrapersonal mediators include: self-efficacy; enjoyment and preference; sports competency; TV viewing style (e.g., channel surfing, selective viewing); benefits and barriers; and beliefs. Interpersonal mediators include: social norms; rules; social support in the neighborhood, at school, and at home; and parental modelling. Environmental mediators include: perceptions of the school environment; access and availability; and policy. These measures have been previously developed and have acceptable psychometric properties and predictive validity [52,56-58,73-78].

##### Moderators

Although not powered to conduct moderating analyses, exploratory analyses will examine moderating effects of sex of the child, parental country of birth, and parental education attainment.

##### Confounders

###### Sociodemographic characteristics

Child's age and sex, family structure (e.g., siblings, number people living in household), parents' age, sex, marital status, education attainment, postcode, and country of birth will be collected in the parent survey. Children will report the number of working cars their family has, the number of holidays they went on in the last year and if they have their own bedroom to assess sociodemographic position [79].

###### General health and family history

The responding parent will report the general health status of their child, and the medical history and family risk factors for diabetes and cardiovascular disease risk factors and their own height and weight.

###### Nutritional intake

Parent proxy-report food/drink frequency questions derived from food items previously identified from the National Nutrition Survey for the target age groups (8-12 years) as important contributors to energy and fat intakes, and thus the energy density of the diet, will be included (items include sweet and savoury snacks and high energy drinks) [80]. Literature supports the accuracy of parent reports of usual food intakes [81].

###### Stage of pubertal maturation

Since all children will be aged 8-9 years old at baseline, it is expected that they will all be pre-pubertal and thus the assessment of pubertal status is not considered necessary. However, to account for any potential growth (maturity) effects, growth rates (change in height) will be assessed from the height measurements taken at each assessment time point.

### Economic Evaluation

An economic evaluation will be undertaken to determine whether Transform-Us! is cost-effective. A societal perspective will be adopted, such that all costs and outcomes will be identified and valued regardless of who bears the cost, receives the benefits or provides the resources [82,83]. Three methods for collecting resource use data will be applied: a diary will be given to teachers to capture any extra preparation time or equipment needed to implement the intervention strategies; an item on the parent survey will capture how much time family members participate in completing school homework tasks; and project monitoring processes will be used to capture other resources used that are pertinent to implementation. Diaries will be completed each day for four weeks throughout the intervention period and at follow-up.

### Process Evaluation

Throughout the intervention (2010 and 2011), the project team will maintain regular contact with teachers. We will monitor the intervention delivery quantity (how many children participated in the various lessons) and quality (that the intervention was delivered as it was intended and any modifications to provided materials) throughout the intervention (teachers to record and rate lessons delivered, sections of class lessons completed with children, number of children present, engagement of the children). In addition to annual interviews with key personnel in the school (e.g., teachers, co-ordinators), we will make unannounced visits to schools to ensure that the teachers understand the intervention delivery requirements, to solve any difficulties or concerns, and to ensure that they are delivering the intervention as intended.

Subjective evaluations of intervention components will also be provided by children, parents and teachers throughout the intervention. At the mid- and post-intervention assessments, teachers will be asked to report on the lesson delivery (e.g., did you deliver the key learning messages, ease with which they were embedded in current curriculum, ease of delivery) and school-based strategy implementation (e.g., were you successful in getting students to complete standing lessons? Was the sporting equipment made available at recess/lunchtimes?). At the post-intervention assessments, teachers who were involved in year one, but not year two, of the intervention will be asked about their continuation of any of the strategies. At the 12-month follow-up assessments, all teachers who have been involved in the SB-I or SB+PA-I intervention in year one and/or year two will be asked to complete a survey to examine maintenance of the class based strategies (i.e., are you still conducting standing lessons?). The uptake of the intervention by teachers not previously involved in year one or two will also be determined.

At the mid- and post-intervention assessments, all participating children will be asked to describe what they know about Transform-Us!. Children in the three intervention groups will be asked to rate how they feel about the school-based components specific to their intervention group (e.g., standing while completing work, availability of sports equipment at recess/lunchtimes); and the home-based components specific to their intervention group (e.g., standing homework tasks, active family pastimes). At the mid- and post-intervention assessments, parents will be asked about the newsletters (e.g., number received, usefulness and their use of strategies to change their child's behavior contained within the newsletters).

### Data analysis

All statistical analyses will be performed using Stata 9.1 for Windows (StataCorp LP) and will adjust for clustering by observations by school (the unit of randomization). All analyses will be conducted using the intention to treat principle. Generalized Estimating Equations (GEE) [84] will be used to fit regression models to describe the effects of the intervention on key outcome variables among children. Separate models will be fitted to determine differences in key outcome variables in the intervention and control groups.

Separate models will be evaluated for each assessment point (mid-intervention; post-intervention; 12 months follow-up), adjusting for baseline levels of the outcome, and, where appropriate, baseline levels of the mediating variables. PA-I and SB-I intervention conditions will be the predictors of primary interest (entered in the form of two indicator variables and their interaction term). Analyses will be performed excluding and including children who were recruited to the study after baseline. For physical activity outcomes, we will compare the PA-I and SB+PA-I versus the SB-I and C groups. For sedentary behavior outcomes, we will compare SB-I and SB+PA-I versus the PA-I and C groups. For health outcomes, we will compare C versus the other three groups and the SB+PA-I versus the single intervention groups. All models will be adjusted for measured confounders. As it has been argued that adjustment for multiple comparisons should not be used when assessing evidence about specific hypotheses no adjustment for multiple comparisons will be performed [85]. To evaluate the magnitude and direction of the intervention effects mediated by intrapersonal, interpersonal and environmental processes, the product-of-coefficient method will be used [86]. A first set of GEE regression models will assess the impact of the intervention condition (regression coefficient α) on the residualized change score of the hypothesized mediators (Table 1), after controlling for significant covariates. A second set of GEE regression models will estimate the independent effects of the intervention condition and residualized changes in the mediators (regression coefficient β) on changes in the outcome variables. The significance of the product of the regression coefficients α and β (representing the mediated effect of the intervention) will be tested using bias-corrected bootstrap methods as outlined by Pituch and colleagues [87].

For the economic evaluation, pathway analysis will be used to identify component activities of the intervention in order to ascertain the associated resource utilization. The cost-effectiveness analysis will measure differential costs between the three intervention groups and C in relation to the outcomes, and intervention costs will be assessed as additional expenditure (savings) against C, expressed as an incremental cost-effectiveness ratio. Incremental cost-effectiveness ratios will be calculated as the cost AUD per BMI unit 'saved' and Disability-Adjusted Life Years (DALYs) 'saved'. The intervention will be modelled for one year as if applied to the Victorian population of children in the target group. The time horizon for measuring the associated health-care cost-offsets and DALY benefits will be the rest of life or 100 years. The reference year will be 2010. The interventions will be run through a model, developed as a part of the ACE-Obesity study, which converts BMI changes to DALY benefits and cost-offsets saved over the lifetime of the cohort [88]. The ACE-Obesity methodology will guide the evaluation to allow cost-effectiveness results to be directly comparable to those of the 13 interventions previously evaluated [89].

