**Methods/design:**

A four-arm cluster-randomized controlled trial (RCT) with a 2 × 2 factorial design, with schools as the unit of randomization. Twenty schools will be allocated to one of four intervention groups, sedentary behavior (SB-I), physical activity (PA-I), combined SB and PA (SB+PA-I) or current practice control (C), which will be evaluated among approximately 600 children aged 8-9 years in school year 3 living in Melbourne, Australia. All children in year 3 at intervention schools in 2010 (8-9 years) will receive the intervention over an 18-month period with a maintenance 'booster' delivered in 2012 and children at all schools will be invited to participate in the evaluation assessments. To maximize the sample and to capture new students arriving at intervention and control schools, recruitment will be on-going up to the post-intervention time point. Primary outcomes are time spent sitting and in PA assessed via accelerometers and inclinometers and survey.

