### Sample size calculations

It is expected that the intervention effects on behavioral and biological primary outcomes will be moderate in size (standardized difference ~ 0.32, equivalent to a mean change in objectively-measured PA of 8 minutes per day [SD = 18 min] and a change in body mass index (BMI) units (age-sex difference from population norm data) of 1.9 kg/m^2 ^[SD = 0.25]) [25,46]. Without accounting for school cluster effects, the number of participants needed to detect a standardized difference of 0.32 with 0.8 power for sedentary behavior (SB-I) and physical activity (PA-I) alone and in combination (SB+PA-I), using a significance level of 0.05 with a two-tailed test, assuming a retention rate of 91% (based on the team's previous experience) and 20 participating schools, would be 340 in total (17 per school). With a previously observed school clustering effect of 0.018 (intra-class correlations [ICCs] for sedentary behavior, physical activity and BMI outcomes estimated using data from a previous intervention study)[44], the minimal total number of participants needed is 520, i.e., 26 per school. Hence, we will conservatively recruit 30 participants per school, giving a total sample size of 600 participants.

Moderate mediated effects of the intervention on the behavioral outcomes are expected (here a moderate mediated effect size is defined as standardized regression coefficients α and β of ~ 0.39)[47]. According to a 2007 simulation study by Fritz and MacKinnon [48], to detect a moderate mediated effect size with 0.8 power, using a significance level of 0.05 with a two-tailed test and bias-corrected bootstrap methods, ~ 61 independent observations are needed. If we assume a 9% rate of loss to follow-up, an average school cluster effect of 0.03 for the mediators (ICCs estimated using data from a previous intervention study)[44] and an average of 30 observations per school (see above), the sample size needed to detect a moderate mediated effect size would be 100 (20 per school). Hence, the sample size needed to detect moderate intervention effect sizes with 0.8 power for the primary outcomes (n = 600) will also be sufficient to detect a moderate-sized effect with 0.8 power for the mediating variables.

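### GEE on 20 schools with no small-cluster correction stated: under ordinary Wald inference, nominal 5% tests run at about 8–12% for the behaviour contrasts and 10–15% for the health contrasts

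*Protocol article*

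**What the plan says.** The abstract of the protocol article gives the number of randomized units: "Twenty schools will be allocated to one of four intervention groups". Equal allocation is implied but not written.

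The Data analysis section states that all analyses "will adjust for clustering by observations by school (the unit of randomization"), in Stata 9.1, and that "Generalized Estimating Equations (GEE) [84] will be used to fit regression models to describe the effects of the intervention". The PA and SB conditions are "entered in the form of two indicator variables and their interaction term", with adjustment for the baseline outcome and measured confounders. The section names two comparisons for behaviour (the two PA arms v the other two; the two SB arms v the other two) and two for health outcomes (C v the other three arms; SB+PA-I v the single-intervention arms).

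It does not name a variance estimator, a working correlation, a reference distribution or any allowance for few clusters. The bias-corrected bootstrap mentioned there applies only to the mediated effect.

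**The concern.** GEE inference is justified by a large number of clusters. Schools were randomized, so the information on treatment comes from 20 units however many children are measured. Two errors then work in the same direction:

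- The sandwich variance is built from residuals that the fitted school-level terms have already shrunk, so it is too small on average.
- A normal cut-off ignores that the variance is estimated from few schools.

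If neither is corrected, false-positive rates exceed the nominal 5% and the intervals are too short. The trial is intended to inform educational policy, so intervals that overstate precision would matter. The health contrasts, which set a single five-school arm against ten or fifteen schools, are the most exposed under the sandwich.

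**Working it through.** **Inputs from the protocol article.** 20 schools in four arms; ICC ("With a previously observed school clustering effect of 0.018"); effect and power ("needed to detect a standardized difference of 0.32 with 0.8 power"); test and retention ("using a significance level of 0.05 with a two-tailed test, assuming a retention rate of 91" per cent); school size ("we will conservatively recruit 30 participants per school, giving a total sample size of 600 participants"). After 9% loss, 546 children are analysed, 27.3 per school.

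**The plan's own figures.**
- n per half of the factorial = 2(1.96 + 0.842)² / 0.32² = 153.3, so 154, or 308 in total.
- 308 / 0.91 = 338.5, rounded up to 17 × 20 = 340, as stated.
- Design effect 1 + 29 × 0.018 = 1.522; 340 × 1.522 = 517.5, rounded up to 26 × 20 = 520, as stated.

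Both reproduce, using normal quantiles and no allowance for school degrees of freedom.

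**Analytic check of test size.** The stated model has four school-level parameters (intercept, PA, SB, interaction), so df = 20 − 4 = 16.
- The 1.96 cut-off with an unbiased variance: P(|t₁₆| > 1.96) = 6.8%.
- Adding the sandwich bias, about √(16/20) = 0.894: P(|t₁₆| > 1.96 × 0.894) = 9.9%.
- Interval width relative to a correct one: 0.894 × 1.96 / 2.12 = 0.83, about 17% too short.

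**Simulation under the null.** Assumptions: 20 schools, five per arm, ICC 0.018, Gaussian outcome, exchangeable working correlation; model with PA, SB, PA × SB, baseline and one child-level covariate. School size is fixed at 27 or varies from 12 to 45 (the variation is assumed). There were 5,000 replicates per setting, with Monte Carlo standard error about 0.4 points at 10%. The table gives the rejection rate of a nominal 5% test. KC is Kauermann-Carroll and MD is Mancl-DeRouen.

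| Contrast | School size | Model-based, z | Sandwich, z | Sandwich × K/(K−1), z | KC, t(16) | MD, t(16) |
|---|---|---|---|---|---|---|
| 10 v 10 | 27 | 9.8% | 10.0% | 9.0% | 4.9% | 3.2% |
| 10 v 10 | 12–45 | 11.0% | 11.4% | 10.6% | 6.0% | 3.6% |
| C v other three | 27 | 10.2% | 12.2% | 11.3% | 7.1% | 4.5% |
| C v other three | 12–45 | 11.0% | 13.2% | 12.5% | 7.7% | 4.9% |
| SB+PA-I v singles | 27 | 9.3% | 11.0% | 10.3% | 5.8% | 3.7% |
| SB+PA-I v singles | 12–45 | 11.9% | 13.9% | 13.1% | 7.5% | 4.3% |

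**Sensitivity.** A separate set of runs (3,000 replicates per setting) also truncated negative ICC estimates at zero and used an independence working correlation. With the K/(K−1) sandwich it gave 8.2–10.2% for 10 v 10 and 10.8–12.7% for the health contrasts. Model-based standard errors gave about 8% under truncation. Estimated standard errors were about 0.86–0.91 of the true sampling SD with the sandwich. At ICC 0.05 and 0.15 the error was 9–13%. Without the interaction term it was 7–8%. The one setting near nominal had an ICC of practically zero with truncated model-based standard errors (about 4.5%), which is not the protocol's ICC.

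**Power of the pooled contrast at 600 recruited.** Design effect 1 + 26.3 × 0.018 = 1.473; effective n per half 273 / 1.473 = 185.3; noncentrality 0.32 / √(2/185.3) = 3.08. The normal reference gives 0.87; t with 16 or 18 df gives 0.82 or 0.83.

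**The case against.** The strongest objection is that the article does not state the error. A reader might infer that the plan prescribes a normal reference or an uncorrected sandwich. It prescribes neither, because the Data analysis section does not address them. Variance corrections and degrees of freedom are often left to a statistical analysis plan, which may exist here and could cure the problem. That stands as a limit: the figures above are conditional on ordinary Wald inference.

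It does not dispose of the point. The section is specific about software version, estimator, model terms, contrasts, its stance on multiplicity and the bootstrap for mediation. It fixes a large-cluster method for a trial it describes as having 20 schools, and nothing in it protects the intervention contrasts.

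Three stronger readings are also unsupported:
- Error rates quoted for a single arm against control would describe a model coefficient, not a comparison that the section names.
- Larger inflation from adding area-disadvantage (SEIFA) strata as covariates would describe a model the article does not state. SEIFA appears only in school selection, and the listed confounders are child and family variables.
- It is too uniform to say that every test's error is doubled. The size depends on the contrast and on unstated working choices.

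Declining multiplicity adjustment is a separate matter and adds nothing to this one.

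**Conclusion.** The point holds in conditional form. With 20 schools and GEE, and absent a small-cluster correction, a nominal 5% test has a true size of about 8–12% for the primary 10 v 10 behaviour contrasts. For the two named health contrasts it is about 10–15% with sandwich standard errors (10–14% in the runs shown) and about 8–12% with model-based ones. Coverage of 95% intervals is about 86–92%. The direction was the same in every setting at the protocol's ICC or above.

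This rests on five schools per arm, the four-parameter factorial model, a normal reference, and the school-size spread assumed above. It does not call the sample size into question: 340 and 520 reproduce, and 600 leaves adequate power for the pooled contrast under a t reference.

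**What to change.** Keep GEE, and state that inference on the intervention contrasts uses a small-sample-corrected sandwich with a t reference on 20 minus the number of school-level parameters (16 df for the stated model). The choice of correction involves a trade-off:

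- **Kauermann-Carroll** gives about 5% for the 10 v 10 contrasts and 6–7% for the health contrasts when schools are of equal size. It rises to 6% and just under 8% when sizes vary from 12 to 45.
- **Mancl-DeRouen** holds the level throughout, at about 3–5%, and is somewhat conservative.

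A linear mixed model with a school random intercept and Kenward-Roger degrees of freedom is an alternative; it was not simulated here. In either case, name a school-level t test or a permutation test as confirmation. State the working correlation and the number of schools per arm at the same time.

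The cost is analysis wording and slightly wider intervals. Power for the pooled contrast is about 0.82–0.83 instead of 0.87 with 546 children analysed, so no additional schools or children are needed to meet the planned 0.80 for that contrast.
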